#### Baseline data

Baseline characteristics will be shown as mean ± standard deviation (SD) for continuous data including age, previous duration, and so on. As for participants' gender, n (%) of male and female in each group will be shown as baseline characteristics. We will conduct between-group comparison in baseline using two-sample t-test or Wilcoxon rank sum test for continuous data and using Chi-square test or Fisher's exact test for gender composition considering p < 0.05 as statistically significant.

If any imbalances in baseline characteristics between groups are encountered, we will conduct ANCOVA (analysis of covariance) using these imbalanced variables as covariates and allocated group as fixed factor.

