### Outcome measures

#### Primary outcome

At present, the goal of asthma care is to achieve and maintain control of clinical manifestation of the disease [27,28]. Hence, we use Asthma Control Test (ACT) to quickly access asthma control, a simple 5-question tool that is completed by the patient and parents/caregivers and recognized by the National Institutes of Health (Table 1)[29,30]. Patients should write the number of each answer in the score box provided, and then add up each score box for your total. ACT will be assessed before treatment and at days 15, 30, 60, and 90 in the treatment period. Follow-up visit will be at 3, 6 months after the last treatment session.

**Table 1 T1:** Asthma Control Test (ACT) for people 12 yrs and older.

1. In the past 4 weeks, how much of the time did your asthma keep you from getting as much done at work, school or at home?					Score
All of the time ①	Most of the time ②	Some of the time ③	A little of the time ④	None of the time ⑤	

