### Statistical methods

#### Statistical analysis plan

We will conduct analysis on an intention-to-treat basis, including all randomized participants with at least one measurable outcome report. Analyses will be conducted using 2-sided significance tests at the 5% significance level. An analysis using the Cochran-Mantel-Haenszel procedure will be done to asses center effect. The statistician conducting the analyses will remain blind to treatment group and data will only be unblinded once all data summaries and analyses are completed. All analyses will be conducted in the SAS statistical package program (ver. 9.1.3).

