#### Outcome data

For primary and secondary outcome measures, these will be summarized descriptively (mean, SD, median, minimum and maximum) at each time point by treatment group. The t-test, Mann-Whitney U and Wilcoxon test were used for comparison of variables, as appropriate.

All adverse events reported during the study will be included in the case report forms; the incidence of adverse events will be calculated. The percentage of subjects with adverse events in each group will be calculated and compared using the chi-squared test or Fisher's exact test.

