#### Sample size

We wished to estimate the sample size according to non-inferiority clinical trial between the heat-sensitive and drug group. Sample size depends on the level of confidence chosen, the risk of type II error (or desired power), and δ. The parameter margin of non-inferiority δ can be specified as a difference in means or proportions. It is often chosen as the smallest value that would be a clinically important effect. To determine δ, we carried out a small sample pilot study previously. The primary endpoint chosen was ACT. The result of outcome showed difference in means between the two groups approximately was 0.45. The choice of δ = 0.15 (30% of Δ) appeared to be reasonable based on clinical relevance and statistical judgment.

If we apply a two-sided 5% significance level(δ = 0.15, α = 0.05, β = 0.2), 95% power the calculated required sample size is approximately 120 participants in each group, according to the following equation. Allowing for a 20% loss to follow up, a total of 144 participants will be required in each group, with 288 participants in total.

$$n=2\times \frac{{\left(U_{\alpha }+U_{\beta }\right)}^{2}}{\gamma^{2}}\times P(1-P)$$

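### Baseline ACT enters the primary comparison only when a chance imbalance triggers it, which gives up precision that pre-specified adjustment would keep

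*Protocol article*

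**What the plan says.** Under Baseline data, the protocol article compares the groups on baseline characteristics with t, Wilcoxon, chi-square or Fisher tests and takes p < 0.05 as significant. It continues: "If any imbalances in baseline characteristics between groups are encountered, we will conduct ANCOVA (analysis of covariance) using these imbalanced variables as covariates". Allocated group is the only fixed factor it names for that model.

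Under Outcome data, the default comparison is given as "The t-test, Mann-Whitney U and Wilcoxon test were used for comparison of variables, as appropriate". None of these tests uses a covariate. Follow-up data places the primary ACT comparison at 3 months.

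Baseline ACT is available. Under Primary outcome: "ACT will be assessed before treatment and at days 15, 30, 60, and 90 in the treatment period". No section makes it a term in the 3-month comparison, and it is not among the baseline variables named as examples (age, previous duration, gender).

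Centre appears in one sentence of the Statistical analysis plan section: "An analysis using the Cochran-Mantel-Haenszel procedure will be done to asses center effect". The Design section lists 12 centres and does not describe randomisation as stratified by centre.

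**The concern.** Under randomisation a baseline significance test asks whether a difference that is known to be due to chance is due to chance. Its result says nothing about which covariates predict the outcome, and prediction is the reason to adjust. A rule driven by that test leaves a prognostic baseline measurement out of the model nearly every time. If some other variable trips the trigger, only that variable enters, so baseline ACT still stays out.

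At stake is the precision of the main result. The baseline score is collected from every participant and can be used at no cost. The rule uses it rarely, so the confidence interval for the ACT difference is wider than it needs to be.

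A secondary point concerns centre. A Cochran-Mantel-Haenszel (CMH) analysis tests the association between group and outcome, stratified by centre. It does not estimate a centre effect, so for ACT it does not do what the article says it is for.

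**Working it through.** **Inputs from the article**
- Two-sided 5% tests (Statistical analysis plan): "Analyses will be conducted using 2-sided significance tests at the 5% significance level".
- About 120 per group before loss to follow-up (Sample size): "If we apply a two-sided 5% significance level(δ = 0.15, α = 0.05, β = 0.2), 95% power the calculated required sample size is approximately 120 participants".
- Baseline threshold p < 0.05 (Baseline data).

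**Inputs not in the article, assumed with a range**
- Correlation rho between baseline and day-90 ACT: 0.2 to 0.7.
- Share of ACT variance lying between centres (ICC): 0.02 to 0.10.
- Equal ACT variance at baseline and day 90 (needed only in step 4).
- When triggered, the ANCOVA replaces the unadjusted test.

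**1. The plan's own figure.** The 120 per group cannot be derived from the stated inputs. The formula 2(Uα + Uβ)² P(1 − P)/0.15² needs a P that is not given. With two-sided 5% and 80% power, 120 requires P of about 0.22. The sentence also gives both β = 0.2 and 95% power. That is a separate matter. Here 120 per group serves only as a sample size, and 80% (β = 0.2) as the reference power of the unadjusted test.

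**2. How often the rule brings in baseline ACT.** Under randomisation a p < 0.05 test fires in 5% of trials by construction. Simulation gave 4.6% to 5.3%. This assumes that baseline ACT is among the variables tested.

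**3. Variance and power, against an unadjusted day-90 comparison.** ANCOVA on baseline multiplies the variance by 1 − rho². If the unadjusted test has 80% power, the ANCOVA power is Φ[(1.960 + 0.842)/√(1 − rho²) − 1.960]. At rho = 0.5: 2.802/√0.75 = 3.235; 3.235 − 1.960 = 1.275; Φ = 89.9%. The sample size for equal power is 120 × (1 − rho²), rounded up.

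The last four columns are simulated: 120 per group, 10,000 trials per scenario, with an effect that gives the t-test about 80% power (no effect for the type I error). The rule uses ANCOVA only if the baseline t-test has p < 0.05.

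| rho | 1 − rho² | n per group for equal power | ANCOVA power (formula) | t-test power | Plan's rule power | Pre-specified ANCOVA power | Type I error of plan's rule |
|---|---|---|---|---|---|---|---|
| 0.2 | 0.96 | 116 | 81.6% | not run | not run | not run | not run |
| 0.3 | 0.91 | 110 | 83.6% | 79.6% | 79.9% | 82.9% | 4.7% |
| 0.5 | 0.75 | 90 | 89.9% | 79.5% | 80.5% | 89.5% | 4.6% |
| 0.7 | 0.51 | 62 | 97.5% | 80.3% | 82.1% | 97.5% | 3.3% |

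Pre-specified ANCOVA held a type I error of 4.8% to 5.1%. The rule gains at most about 2 percentage points of power over the plain t-test (82.1 − 80.3 = 1.8) and leaves most of the available gain unused.

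**4. If the t-test is meant for change scores.** Its variance factor is 2(1 − rho), against (1 − rho)(1 + rho) for ANCOVA, a ratio of (1 + rho)/2. At rho = 0.2, 0.5 and 0.7 the ANCOVA variance is 0.60, 0.75 and 0.85 of the change-score variance. ANCOVA is more precise for any rho below 1.

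**5. Centre alone.** A centre term multiplies the variance by about 1 − ICC. From 80% power this gives 80.8% at ICC 0.02, 82.0% at 0.05 and 84.0% at 0.10.

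**The case against.** **The size is not documented.** No correlation, SD or ICC is given. Eligibility is limited to one severity grade, which could lower the correlation; at 0.2 the variance falls by only 4%. This stands, and it is why a range is shown. The direction holds for any correlation other than zero.

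**The trigger is an inference.** The word imbalances is not defined in its own sentence. Reading it as p < 0.05 from the sentence before is the natural reading, not the only one. If it is not p-based, the trigger is undefined.

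**Baseline ACT may be used after all.** The article does not say whether the tests use the 3-month score or the change from baseline, so it cannot be said flatly that baseline ACT is ignored. Step 4 shows that change scores would still be less precise than ANCOVA.

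**An unseen analysis plan may settle this.** It may, but the article states a specific rule, and the point is about that rule.

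**Stronger readings that the document does not support**
- A reader might infer that a model chosen from the data biases the result or inflates the type I error. The simulated error is 3.3% to 4.7%, so the rule is conservative. It selects on baseline data, not outcomes, and the statistician is to be blind to group.
- A reader might set an unflagged baseline gap against δ = 0.15. With an assumed SD of 3 and 144 per group, the largest gap escaping the test is 1.96 × 3 × √(2/144) = 0.69 point. At rho 0.4 to 0.6 it shifts day-90 ACT by 0.28 to 0.42. That is a worst case on an undocumented SD. Chance imbalance is already in the t-test's standard error, whose 95% half-width on the same inputs is also 0.69. The article also pairs δ with a proportion formula, so it is a poor yardstick here.
- A reader might say that 40% of trials would show some imbalance (1 − 0.95¹⁰). That rests on ten independent tests, a count the article does not give.
- A reader might think that leaving out centre invalidates the comparison. Randomisation is not described as stratified by centre, so the cost is precision only, and it is modest.

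**Conclusion.** The point holds as a loss of efficiency. The stated rule makes adjustment for baseline ACT a chance event of about 5%, and it recovers little of the precision that the data offer. For assumed correlations of 0.2 to 0.7, pre-specified adjustment would reduce the variance of an unadjusted day-90 comparison by 4% to 49%. At 0.5, simulated power is 89.5% against 80.5% under the plan's rule. The power figures start from an unadjusted test with 80% power at 120 per group; the variance factors do not depend on that starting point. The planned comparison remains valid but is weaker than it need be. The CMH point is secondary: the procedure does not estimate a centre effect, and adding centre alone brings power from 80% to about 81–84% at the assumed ICCs. The change should be made, but the trial's validity does not hang on it.

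**What to change.** Replace the conditional rule with one primary model fixed in advance: ANCOVA of day-90 ACT with group and baseline ACT as terms and centre (12 levels) as a fixed factor. Report the adjusted mean difference with its 95% CI. Present baseline characteristics descriptively, and do not let significance tests decide what is adjusted for.

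For ACT, replace the CMH analysis with the centre term in this model, and add a group-by-centre term as an exploratory analysis. CMH can be kept for binary outcomes such as adverse-event incidence.

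The cost is a change of wording in the Statistical analysis plan, Baseline data and Outcome data sections. Baseline ACT and centre are already recorded; no extra participants, visits or data are needed.

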#### Outcome data

For primary and secondary outcome measures, these will be summarized descriptively (mean, SD, median, minimum and maximum) at each time point by treatment group. The t-test, Mann-Whitney U and Wilcoxon test were used for comparison of variables, as appropriate.

All adverse events reported during the study will be included in the case report forms; the incidence of adverse events will be calculated. The percentage of subjects with adverse events in each group will be calculated and compared using the chi-squared test or Fisher's exact test.

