
## Method/design

### Objective

The aim of this study is to investigate the effectiveness of heat-sensitive moxibustion compared with fluticasone/salmeterol (seretide) in patients with chronic moderate persistent asthma in China.

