## Discussion

To our knowledge, the goal of asthma care is to achieve and maintain control of clinical manifestations of the disease for prolong periods. When asthma is controlled, patients can prevent most attacks, avoid troublesome symptoms day and night, and keep physically active [1]. Acupuncture therapy was often perceived as an effective option to control asthma successfully by patients with chronic asthma. The use of acupuncture in asthma patients is increasing as an adjunct and also as a substitute for effective and proven therapies [39]. In China, moxibustion are considered as an ancient treatment to prevent and control asthma, and still widely used today. A number of clinical trial suggested moxibustion as one of traditional acupuncture therapy, should effective in the treatment of asthma. But the methodological problems of published trials haunt us the trust of moxibustion. Therefore, we design this rigorous clinical trials meeting the CONSORT statement and guidelines to guarantee a high internal validity for the results.

At present, various conventional medications are used to slow down and control with the disease. An ICS/LABA combination in a single inhaler represents a safe, effective and convenient treatment option, and recommended by GINA. So, we selected the fluticasone/salmeterol (seretide) as the control treatment in the protocol. Actually, the aim of this trial is to search an effective CAM treatment to control asthma, as good as conventional drug. The focused features of moxibustion are low cost, less adverse event and low risk.

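### The trial is sized for non-inferiority on ACT, but the stated primary analysis is a two-sided test of no difference that never uses the margin

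*Protocol article*

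**What the plan says.** All references are to the protocol article.

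- **Sample size:** "We wished to estimate the sample size according to non-inferiority clinical trial between the heat-sensitive and drug group". The primary endpoint is ACT. On the margin: "The choice of δ = 0.15 (30% of Δ) appeared to be reasonable based on clinical relevance and statistical judgment". The result is 120 per group, raised to 144 per group (288 in total) for 20% loss.
- **Discussion:** "the aim of this trial is to search an effective CAM treatment to control asthma, as good as conventional drug".
- **Objective:** an investigation of effectiveness in comparison with fluticasone/salmeterol. No type of hypothesis is named.
- **Statistical analysis plan:** "Analyses will be conducted using 2-sided significance tests at the 5% significance level". The set is all randomised participants with at least one measurable outcome.
- **Outcome data**, for primary and secondary outcomes alike: group summaries (mean, SD, median, range) at each time point, then "The t-test, Mann-Whitney U and Wilcoxon test were used for comparison of variables, as appropriate".
- **Follow-up data:** the primary analysis compares the two groups on ACT at 3 months. No criterion is given for what the comparison has to show.

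δ appears only in the Sample size section. None of the analysis sections mentions a margin, a confidence interval, a direction or a non-inferiority criterion.

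**The concern.** The design and the analysis answer different questions. A non-inferiority trial tries to reject the hypothesis that the new treatment is worse by δ or more. The tests named under Outcome data try to reject the hypothesis of no difference. Failing to reject that second hypothesis says nothing about whether a deficit of δ has been ruled out, and failure becomes more likely as the data get noisier.

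At stake is the primary conclusion. If the arms are truly similar, the usual outcome of the stated test is p > 0.05. The plan then has no rule that leads from that result to the aim in the Discussion. Any rule chosen after the data are seen would carry little weight. The comparator is a combination inhaler that the article itself presents as mainstay treatment, so an unsupported claim of parity would have consequences.

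**Working it through.** **Inputs from the article:** δ = 0.15; 120 per group before allowance for loss and 144 after; two-sided α = 0.05; β = 0.2, with 95% power named in the same sentence.

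**Inputs assumed:** the SD of ACT is not given, so I use 1, 2, 3 and 4 points. δ is read as ACT points, since the Sample size section reports the pilot result as a difference in means.

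**1. The plan's own figure.** The 120 cannot be reproduced, because neither P nor an SD is stated. The displayed formula is n = 2(Uα + Uβ)²/γ² × P(1 − P). With γ = 0.15, two-sided 5% and β = 0.2:

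- 2 × (1.960 + 0.842)² / 0.15² = 697.7
- 120 / 697.7 = 0.172, so P would have to be about 0.22 or 0.78
- if δ is a difference in means, SD² takes the place of P(1 − P), and the SD would have to be √0.172 = 0.415 ACT points

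The section therefore pairs a difference in means with a formula for proportions, and the scale of δ is left open.

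**2. The stated test when moxibustion is worse by exactly δ.**

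SE = SD × √(2/n)

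P(non-significant) = 1 − [Φ(D/SE − 1.96) + Φ(−D/SE − 1.96)], with D = 0.15

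| Assumed SD | SE, n = 120 | Non-significant, n = 120 | SE, n = 144 | Non-significant, n = 144 |
|---|---|---|---|---|
| 2 | 0.258 | 91% | 0.236 | 90% |
| 3 | 0.387 | 93% | 0.354 | 93% |
| 4 | 0.516 | 94% | 0.471 | 94% |

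Both sizes are shown because the stated analysis set, with last observation carried forward, could hold up to 144 per group.

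**3. The matching rule at the same true deficit.** Non-inferiority is concluded if the estimate minus 1.96 × SE exceeds −0.15. With a true difference of −0.15, this happens with probability 1 − Φ(1.96) = 2.5%, whatever the SD.

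**4. What the matching rule would deliver at a true difference of zero, n = 120.**

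Half-width of the 95% CI = 1.96 × SD × √(2/120) = 0.253 × SD

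Power = Φ(0.15/SE − 1.96)

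| Assumed SD | Half-width (points) | Power |
|---|---|---|
| 1 | 0.253 | 21% |
| 2 | 0.506 | 8% |
| 3 | 0.759 | 6% |
| 4 | 1.012 | 5% |

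**The case against.** **The article does not declare non-inferiority throughout.** The Objective speaks only of a comparison with the drug, and Follow-up data speaks of differences being maintained. This is fair: the sections conflict on the type of hypothesis. It supports the need to reconcile them, because the sample size rests on non-inferiority alone.

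**The ingredients are there.** Means and SDs by group will be reported, and a two-sided 5% level corresponds to a 95% interval that could be set against δ. A rank test can also be inverted to give a Hodges-Lehmann interval in ACT points under a location shift. All this stands, so the trial's data could answer the question. What is missing is a stated rule that does so.

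**A condensed article may leave the rule to a fuller plan.** This has less force here, because the article has a section headed as the analysis plan and names the tests for the primary outcome. A later plan would have to replace that text, not merely add to it.

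Three stronger readings are tempting, and the documents do not support them:

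- *That the investigators will read p > 0.05 as equivalence.* No section says so.
- *That the lack of a per-protocol set is an error.* The article does not exclude one, and an unseen plan may contain it.
- *That the intention-to-treat set with last observation carried forward must favour the non-inferiority claim.* The direction depends on who drops out and when, which the documents do not settle. Earlier dropout on moxibustion could count against it.

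**Conclusion.** The mismatch is in the text and should be corrected before the data are unblinded. The trial is sized to rule out a deficit of δ, and its stated primary analysis tests for no difference without using δ. A significant result favouring moxibustion would imply non-inferiority. A non-significant one would leave the trial's aim unanswered under the plan as written.

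The size of the gap at the plan's own margin is a non-significant result in roughly 90% to 94% of trials, against a false-claim rate of about 2.5% under an interval rule. These percentages rest on assumed SDs of 2 to 4 and on δ being in ACT points. The 90% to 94% is the chance of a result from which parity might wrongly be inferred. It is not a false-claim rate that the protocol has adopted. The conflict between sizing and analysis does not depend on any assumed SD.

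**What to change.** 1. State the primary hypothesis as non-inferiority of ACT at 3 months, expressed as moxibustion minus drug, and bring the Objective into line with it.
2. Conclude non-inferiority only if the lower limit of the two-sided 95% confidence interval for the mean difference lies above −δ. Test superiority only afterwards, from the same interval.
3. Keep the t-test and rank-test p-values as supportive.
4. State δ on the ACT-point scale used in the analysis, and replace the proportion formula with one for means that gives the SD used.
5. A per-protocol analysis is a useful supportive check.

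**Cost.** Items 1 to 3 are wording. The claim becomes harder to reach than with a non-significant difference test. Item 4 is not free: if δ is 0.15 ACT points, the power in step 4 of the working is far below either figure implied in the Sample size section (80% from β = 0.2, or 95%) unless the SD is near 0.4. The stated power must then be restated, and the margin and sample size may have to be reconsidered.

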##### Dropped or missing data

Reasons for dropped or missing data will be explored by descriptively. Missing data will be replaced according to the principle of the last observation carried forward.

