#### Secondary outcomes

Measurement of lung function provides an assessment of the severity, reversibility, and variability of airflow limitation. Forced expiratory volume in 1 s (FEV1) and peak expiratory flow (PEV) will be used in this trial. Attack frequency also will be assessed. These outcomes also will be assessed before treatment and at days 90 in the treatment period. Follow-up visit will be at 3, 6 months after the last treatment session. Adverse event information will be collected at each clinic visit.

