##### Follow-up data

The primary outcome will be the ACT scores. The primary analysis will compare the two groups in 3 months. A secondary analysis will compare the two groups at 6,9 months to assess if any differences between groups have been maintained over time.

Loss to follow-up is likely to lead to biased estimates of intervention effect. We will try to avoid bias due to attrition by carefully following up the participants in both groups. We will phone participants who fail to complete questionnaires after a second reminder. We anticipate a 20% loss to follow-up in this trial, and will implement procedures to minimize loss to follow-up and patient withdrawal, and where possible, we will collect information on reasons for patient withdrawal.

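### Last observation carried forward is the only missing-data rule: it can overstate persistence at 6 and 9 months and can bias the day-90 comparison in either direction

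*Protocol article*

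**What the plan says.** All places are in the Protocol article.

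- **Dropped or missing data.** Reasons for missingness are to be described, and then: "Missing data will be replaced according to the principle of the last observation carried forward". No other method is named, and the rule is not limited to any outcome or visit.
- **Follow-up data.** "We anticipate a 20% loss to follow-up in this trial". The same paragraph concedes: "Loss to follow-up is likely to lead to biased estimates of intervention effect". The measures listed against this are reminders, telephone calls and recording the reasons for withdrawal.
- **Time points (Follow-up data).** "The primary analysis will compare the two groups in 3 months". Then: "A secondary analysis will compare the two groups at 6,9 months to assess if any differences between groups have been maintained over time".
- **Primary outcome.** "ACT will be assessed before treatment and at days 15, 30, 60, and 90 in the treatment period". After that: "Follow-up visit will be at 3, 6 months after the last treatment session". Design gives 90 days of treatment followed by six months of follow-up, so the follow-up visits fall at months 6 and 9, off trial treatment.
- **Secondary outcomes.** For FEV1, peak expiratory flow and attack frequency: "These outcomes also will be assessed before treatment and at days 90 in the treatment period". They have no visit between baseline and day 90.
- **Statistical analysis plan.** The analysis set is every randomised participant with one or more measurable outcome reports. Tests are two-sided at 5%.
- **Sample size.** The trial is sized as a non-inferiority trial with margin 0.15. The pilot difference in mean ACT was about 0.45, and there are 144 participants per group.

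**The concern.** The 6- and 9-month comparisons ask what happens to a difference once treatment has stopped. For a participant last seen at day 90 or earlier, carrying forward answers that question by assumption, because the score at the end of treatment, or before it, stands in for the off-treatment result. Part of any apparent durability would then come from the rule and not from patients.

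The primary day-90 comparison is also exposed. ACT recalls the past four weeks, so a day-15 score still covers about 28 − 15 = 13 days before treatment. Carried to day 90, it is not a day-90 score. The burdens also differ: Treatment protocol gives 8 + 12 + 15 + 15 = 50 moxibustion sessions against a twice-daily inhaler. Unequal dropout is therefore plausible, although the article gives no rates by arm.

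For lung function and attack frequency, the only value before day 90 is the baseline one. Retention effort reduces the amount of missing data but does not repair the analysis of what remains missing. The rule is stated outright in the article, so this is not a detail left to a document that is not shown.

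**Working it through.** The article gives no figure for the effect of carrying forward, so there is none to reproduce. The illustrations below use its own inputs where it has them.

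**Inputs from the article:** 20% loss (one figure, not split by arm or visit); 144 per group; pilot difference 0.45; margin 0.15, read here as ACT points because Sample size derives it from a difference in ACT means.

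**Assumed:** SD of ACT 3; day-90 differences of 1 and 2 points as alternatives to the pilot value; dropouts sharing their arm's mean.

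**1. Months 6 and 9.** Let m be the share in each arm whose day-90 score is carried, and r the share of the day-90 difference that truly persists. The analysis shows the fraction m + (1 − m)r of the day-90 difference.

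| m | r = 0 | r = 0.5 | r = 1 | r = 1.5 |
|---|---|---|---|---|
| 10% | 0.10 | 0.55 | 1.00 | 1.45 |
| 20% | 0.20 | 0.60 | 1.00 | 1.40 |
| 30% | 0.30 | 0.65 | 1.00 | 1.35 |

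Persistence is overstated when the difference wanes (r < 1) and understated when it grows (r > 1). There is no distortion at r = 1.

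Now take m = 20% and r = 0. The standard error is 3 × √(2/144) = 0.354. With spurious difference b and z = b/0.354, the rejection probability of the nominal 5% test is 1 − Φ(1.96 − z) + Φ(−1.96 − z).

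| Day-90 difference | b = 0.2 × difference | z | Rejection |
|---|---|---|---|
| 0.45 (pilot) | 0.09 | 0.25 | about 5.7% |
| 1 | 0.20 | 0.57 | about 8.7% |
| 2 | 0.40 | 1.13 | about 20% |

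**2. Day 90, ACT.** Let A be moxibustion and B the drug, m the share missing in an arm, and g the carried score minus the true day-90 score. The bias in A − B is mA·gA − mB·gB.

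- 20% missing in both arms, equal gaps: 0.
- 20% in both, gA = +2, gB = 0: 0.2 × 2 = +0.40. With gA = −2, gB = 0: −0.40.
- 25% in A and 15% in B, both gaps −1: −0.25 + 0.15 = −0.10. Both gaps −2: −0.50 + 0.30 = −0.20.

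A second illustration assumes true mean gains of 4 (A) and 5 (B), a true difference of −1.0, and dropouts who have reached half the gain:

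- 10% lost in A, 30% in B: (0.9 × 4 + 0.1 × 2) − (0.7 × 5 + 0.3 × 2.5) = 3.80 − 4.25 = −0.45.
- 20% lost in each: (0.8 × 4 + 0.2 × 2) − (0.8 × 5 + 0.2 × 2.5) = 3.60 − 4.50 = −0.90.
- 30% lost in A, 10% in B: (0.7 × 4 + 0.3 × 2) − (0.9 × 5 + 0.1 × 2.5) = 3.40 − 4.75 = −1.35.

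The shifts from the truth are +0.55, +0.10 and −0.35. Both unequal splits shift the result by more than 0.15, in opposite directions.

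**3. Lung function and attack frequency at day 90.** If baseline is carried, each dropout contributes zero change. With true mean changes dA and dB, the estimate is (1 − mA)dA − (1 − mB)dB. Equal 20% loss before day 90 gives 0.8(dA − dB), a shrinkage of 20%. If dA = dB = d but loss is unequal, it gives (mB − mA)d, a difference where none exists.

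**The case against.** Several points on the other side stand and limit the claim.

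- A reader might infer that the rule manufactures a maintained effect. It does not do so by itself. It preserves only the carried share of a day-90 difference, needs such a difference to exist and then wane, and can equally hide a growing one. With the only ACT difference the article reports, 0.45, rejection rises only from 5% to about 5.7%. The 20% rate needs an assumed 2-point difference.
- A participant seen at month 6 and lost by month 9 has an off-treatment score carried. The 20% is one figure for the whole trial, so m = 20% is an upper case at 9 months. The full 20% cannot be lost both before and after day 90.
- A reader might infer that the rule tilts day 90 towards non-inferiority. The documents do not support that. The sign depends on who drops out and when, and all three results in the second illustration, like the true −1.0, lie beyond the 0.15 margin. None shows a false non-inferiority conclusion. The non-inferiority framing also rests on Sample size; the analysis sections state two-sided tests and no non-inferiority rule.
- The article does not say whether baseline counts as an observation to carry. That it would be carried for lung function is inferred from the visit schedule and the analysis set.
- Retention measures are planned and could bring loss below 20%.

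None of this defends the rule for a comparison whose purpose is to test persistence.

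**Conclusion.** The concern holds in a limited form. Carrying forward is the article's sole missing-data rule, and it places treatment-period scores in the off-treatment comparisons for anyone lost before month 6. In the upper case of 20% carried per arm and no true persistence, 20% of the day-90 difference remains: 0.09, 0.2 or 0.4 ACT point for day-90 differences of 0.45, 1 or 2. Rejection is then about 5.7%, 8.7% or 20%, with SD 3 and 144 per arm assumed.

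At day 90 the ACT bias is a risk of unknown sign. It is nil with equal missingness and equal gaps, and larger than 0.15 under modest differences between arms. For lung function and attack frequency, the no-change assumption for early dropouts follows only if baseline is carried.

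The article gives no missingness by arm or visit, so the actual size cannot be fixed. The change should be made because the rule is poorly matched to the question and a better one needs no new data.

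**What to change.** In Dropped or missing data, replace carrying forward as follows.

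- **ACT to day 90:** a likelihood-based repeated-measures model on days 15, 30, 60 and 90 with baseline ACT, centre and group-by-visit terms, reporting the day-90 contrast.
- **Months 6 and 9:** the same model extended to those visits, or multiple imputation, with no treatment-period value carried past day 90.
- **Lung function:** baseline-adjusted ANCOVA or multiple imputation instead of carrying baseline. With a single on-treatment measurement, a repeated-measures model would add little for those lost before day 90.
- **Carrying forward:** keep it at most as a sensitivity analysis.

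The cost is revised analysis wording, modest extra programming and slightly more complex reporting. No visit or measurement is added.
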